**Fig. 1 Fig1:**
[figure not shown]
CONSORT Flow Chart

### Intervention

The intervention as part of this research will continue for eight weeks. In the experimental group, patients will be treated with a dorsal blocking orthosis in a neutral (0° extension) position. In the control group, patients will be treated using buddy loops, where the injured digit is ‘buddied’ to a border digit for support.

Participants in both groups will commence protected early AROM exercises (Fig. 2). For the experimental group, this will entail commencing active isolated Distal Interphalangeal Joint (DIPJ) and PIPJ flexion and extension exercises and then composite flexion and extension exercises within the orthosis. In the control group, this will entail actively flexing and extending all the joints of the injured digit within the buddy loop. Patients will be asked to complete 10 repetitions, 6 times per day. Exercises will be progressed as per treatment guidelines (Appendix 1).

**Fig. 2 Fig2:**
[figure not shown]
Intervention of experimental and control groups

At three weeks after the commencement of treatment, if clinically indicated, both groups will start to wean out of their orthosis or buddy loops but continue to wear them for sleeping and ‘at risk’ activities. At five weeks’ post commencement of treatment, patient will discharge their orthosis or buddy loops if clinically appropriate.

Treatment will be progressed as clinically indicated as per the treatment guideline (Appendix 1) that has been developed to improve consistency among treating therapists. The treatment guideline will be provided to treating therapists and provide clinical scenarios that they might encounter such as ‘good passive but reduced active PIPJ flexion’ and recommended exercises they can implement to address this impairment.

### Data collection

Baseline demographic data will be collected, and the initial assessment will be completed by a blinded hand therapist. Data collection will then be completed at weeks 3, 5 and 8, which will coincide with planned treatment progression (Table 1).

**Table 1 Tab1:** Data collection table

	Initial	3 Weeks	5 Weeks	8 Weeks
Demographics	✓			
**Primary outcome measure**				
PIPJ PROM extension		✓	✓	✓
**Secondary outcome measures**				
MCPJ AROM (^0^) Injured	✓	✓	✓	✓
MCPJ AROM (^0^) Uninjured	✓			
PIPJ AROM (^0^) Injured	✓	✓	✓	✓
PIPJ AROM (^0^) Uninjured	✓			
DIPJ AROM (^0^) Injured	✓	✓	✓	✓
DIPJ AROM (^0^) Uninjured	✓			
TAM (^0^) Injured	✓	✓	✓	✓
TAM (^0^) Uninjured	✓			
MCPJ PROM (^0^) Injured		✓	✓	✓
MCPJ PROM (^0^) Uninjured		✓		
PIPJ PROM (^0^) Uninjured		✓		
DIPJ PROM (^0^) Injured		✓	✓	✓
DIPJ PROM (^0^) Uninjured		✓		
TPM (^0^) Injured		✓	✓	✓
TPM (^0^) Uninjured		✓		
Pain (NRS)	✓	✓	✓	✓
PRWHE	✓	✓	✓	✓
Oedema (cm)	✓	✓	✓	✓
Grip Strength (Kg) Injured			✓	✓
Grip Strength (Kg) Uninjured			✓	
Adherence		✓		
RTW/Usual Everyday Activities	✓	✓	✓	✓
Complications		✓	✓	✓

### Outcome measure

Outcome measures will be gathered at baseline and weeks 3, 5 and 8 after the commencement of treatment (Table 1).

The primary outcome measure will be passive PIPJ extension. Passive PIPJ extension will be assessed in a standardised way as described by American Society of Hand Therapists (ASHT) [18]. Assessment of Passive Range of Motion (PROM) with a goniometer has been shown to be consistently reliable when standardised methods are implemented [18].

Secondary outcome measures for this study will include AROM and PROM of other joints, grip strength, oedema, pain level, function and treatment adherence will be captured.

AROM of all the joints of the injured digit including the Metacarpal Phalangeal Joint (MCPJ), PIPJ and DIPJ. This will be compared to the contralateral uninjured digit and will be undertaken using a single goniometer. In addition to AROM, Total Action Motion will be calculated and compared to the uninjured contralateral digit as per the ASHT guidelines [18].

PROM of all the joints of the injured digit will be compared to the contralateral uninjured digit and will be undertaken using a single goniometer. PROM can provide information about a joint’s capacity for motion [19] and ensure the home exercise program is tailored specifically to the patients’ impairments. In addition, Total Passive Motion will be calculated and compared to the uninjured contralateral digit [18].

Grip strength will be assessed using a standardised Jamar Dynamometer and adopting a standardised testing procedure as per the ASHT guidelines [19]. A single score of maximum effort will be recorded for the injured and uninjured side [20].

Oedema will be assessed using standardised testing procedure as described by ASHT guidelines. A standardised tape measure will be used to take a circumferential measurement of the PIPJ [21] and compared to the contralateral uninjured side.

Pain will be assessed using a Numerical Rating Scale. The patient will be asked to rate their pain between ‘0' and ‘10', with ‘0' describing ‘no pain’ and ‘10’ used to describe ‘worst pain imaginable’. Pain will also be assessed using the pain section of the Patient Rated Wrist and Hand Evaluation (PRWHE), which has been demonstrated to be a valid and reliable assessment of patient rated function and disability and complements the Numerical Rating Scale to assess pain in a holistic way [22].

Function will be assessed using the PRWHE, which has been shown to have good levels of evidence for validity, reliability [23] and responsiveness to trauma [24]. Return to work/everyday activities status will be determined by asking the patient if they have returned to their pre-injury roles, modified role or not at all. The adverse impact of hand injuries on return to work and everyday activities have been reported in the literature [25].

Adherence to treatment will be assessed via a questionnaire developed based on the work of SandfordBarlow [26]. The questionnaire asks the same key questions regarding adherence to treatment such as, if the splint has been removed, how often it may have been removed and why it may have removed but adapted slightly to reflect the different diagnostic group. This will be measured at the three-week assessment point, after this stage, patients will cease wearing the orthosis/buddy loop full time and commence a weaning process.

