### Sample size

A mean difference of 10° in passive PIPJ extension scores between the control and experimental groups is deemed to be clinically relevant. Based on a quality improvement project on volar plate injuries at Sydney Hospital, a standard deviation of 10° in passive PIPJ extension scores is estimated [17]. To be able to detect this difference with 90% power at the 5% significance level, 23 participants will be required in each group. Factoring in a dropout rate of 25% brings the total to 32 participants in each group.

At Sydney Hospital Hand Clinic, there were 149 presentations for volar plate injuries in the period between 22/06/2017 – 18/12/2018. It is anticipated that there will be a 50% uptake of patients consenting to be involved in the study. Therefore, recruitment and data collection is anticipated to take 18 months.

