### Data analysis

Analysis will commence with descriptive statistics. Histograms and descriptive statistics will be used to review the distribution of continuous variables for outliers, skewness and other potential problems. Counts and percentages will be used to review categorical variable for small categories. Scatterplots and side-by-side boxplots will be employed to visually check for associations between variables. Outliers will be checked for data errors and, if legitimate, adjusted for using Winsorizing or trimming. Data transformations will be used to address skewness if required.

Independent samples t-tests will be used review the statistical significance of these differences in means at follow-up. Analysis of covariance (ANCOVA) will be used to adjust for any differences between groups at baseline. Repeated measures analysis of variance (ANOVA-RM) or linear mixed models will be used to model differences between treatment groups over time. Data will be analysed using an ‘intention to treat’ analysis.

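### The uninjured finger's passive PIPJ extension is measured but never enters the between-arm analysis, which forgoes precision in the primary comparison at almost no saving

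*Protocol article*

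**What the plan says.** **Outcome.** The Outcome measure section states: "The primary outcome measure will be passive PIPJ extension". No side-to-side difference is defined.

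**Sample size.** The calculation is on that same score: "A mean difference of 10° in passive PIPJ extension scores between the control and experimental groups is deemed to be clinically relevant", and "a standard deviation of 10° in passive PIPJ extension scores is estimated". It concludes: "To be able to detect this difference with 90% power at the 5% significance level, 23 participants will be required in each group".

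**Uninjured side.** The Outcome measure section says that "PROM of all the joints of the injured digit will be compared to the contralateral uninjured digit". It does not say in what form, or whether this enters the comparison of the two arms. Table 1 lists "PIPJ PROM (^0^) Uninjured" among the secondary outcomes, with one tick, at 3 weeks. Uninjured active motion of the same joint is ticked at the initial visit.

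**Analysis.** The Data analysis section says: "Independent samples t-tests will be used review the statistical significance of these differences in means at follow-up". It adds ANCOVA to deal with baseline differences between groups, and repeated measures ANOVA or linear mixed models over time. No covariate is named and the uninjured digit is not mentioned.

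**Baseline of the primary outcome.** In Table 1, passive PIPJ extension of the injured digit is ticked at weeks 3, 5 and 8. The initial column is empty.

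**The concern.** Comparing a patient's injured finger with the healthy finger on the other hand is a within-patient description. It does not compare the orthosis with buddy loops. The protocol announces the first and plans the second, and nothing links them.

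If passive PIPJ extension differs naturally between people, part of the assumed 10° SD is constitutional and unrelated to injury or treatment. The uninjured contralateral reading can account for that part. Neither treatment acts on that digit, because buddy loops join the injured finger to its neighbour on the same hand. The reading is therefore a legitimate covariate even when taken after randomisation.

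The gap matters more here because the usual covariate, the starting value of the same outcome, is not scheduled. The uninjured passive PIPJ angle is the closest same-measure covariate that the trial collects. What is at stake is the width of the confidence interval for the primary effect and some power, at the price of wording rather than measurement.

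**Working it through.** **Inputs from the protocol (Sample size):** difference 10°, SD 10°, 5% significance level (taken as two-sided, which reproduces the stated figure), 90% power, 1:1 allocation.

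**Inputs assumed:** the correlation r between injured and uninjured passive PIPJ extension, and the SD s_u of the uninjured side. The protocol gives neither, so a range is shown.

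**Step 1: reproduce the plan's figure.** For a two-sample t-test with n per arm, the noncentrality is 10 / (10 × √(2/n)).
- n = 22: 10 / (10 × √(2/22)) = 3.317; power 0.8997, just under 90%.
- n = 23: 10 / (10 × √(2/23)) = 3.391, with 44 degrees of freedom and critical value 2.015; power 0.9125.

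So 23 per arm is right for the unadjusted score. Allowing for 25% dropout gives 23 / 0.75 = 30.7, rounded up to 31; the protocol enrols 32, slightly more.

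**Step 2: add the uninjured angle as a covariate.** Residual SD = 10 × √(1 − r²). The same power calculation is then run at 23 per arm and 10°.

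| r (assumed) | Residual SD | Reduction in standard error | Power, 23 per arm | n per arm for 90% |
|---|---|---|---|---|
| none (unadjusted) | 10.00° | – | 91.2% | 23 |
| 0.1 | 9.95° | 0.5% | 91.5% | 22 |
| 0.3 | 9.54° | 4.6% | 93.5% | 21 |
| 0.5 | 8.66° | 13% | 96.9% | 17 |

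Example: at r = 0.3, 10 × √(1 − 0.09) = 9.54°, and 10 / (9.54 × √(2/23)) = 3.555, which gives 93.5%. The degree of freedom spent on the covariate is ignored in the table; allowing for it changes power by 0.1 percentage point or less.

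**Step 3: why a covariate and not a difference score.** SD of injured minus uninjured = √(10² + s_u² − 2 × r × 10 × s_u). This is below 10° only if r > s_u / 20.
- s_u = 10°, r = 0.3: √(100 + 100 − 60) = 11.83°; power 80.0%.
- s_u = 5°, r = 0: √(100 + 25) = 11.18°; power 84.3%.
- s_u = 5°, r = 0.3: √(100 + 25 − 30) = 9.75°; power 92.5%, against 93.5% with the covariate.

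A regression coefficient adapts to the actual correlation. Subtraction fixes the coefficient at 1 and can lose power relative to ignoring the uninjured side.

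**The case against.** The strongest reply is that this is an optional refinement. The document is a condensed article, a covariate list often sits in an analysis plan, and the models that could carry the covariate (ANCOVA, mixed models) are already named. The trial has about 91% power on its own inputs. The correlation is unknown and may be low: the outcome of interest is contracture after injury, so much of the 10° SD may come from the injury rather than from constitution. The exclusion of patients whose contralateral digit has reduced motion or pain may narrow the uninjured spread further. At r = 0.1 the gain is 0.3 percentage points.

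Most of that stands as a limit on the size of the point. It does not remove the point. The protocol does state an analysis (t-tests, with ANCOVA for baseline differences), and for the primary outcome that ANCOVA has no starting value to work with. Using a reading already on the schedule is a better method than the one stated, not merely extra detail.

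A reader might infer four stronger things, which the documents do not support:
- **That the primary comparison is biased or invalid.** Randomisation balances natural extension in expectation, so the unadjusted comparison of angles is sound.
- **That the protocol rules the uninjured reading out of the primary analysis.** It is silent on its role.
- **That subtraction is planned.** No difference score is described. Step 3 of the working explains the choice of fix and does not describe the plan.
- **That grip is to be compared side to side.** The text only has both sides recorded.

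**Conclusion.** The point holds as missed precision. The between-arm analysis does not use the uninjured passive PIPJ reading, and no initial value of the primary outcome is available in its place. With 23 per arm and a true difference of 10°, adjustment would raise power from 91.2% to between 91.5% (r = 0.1) and 96.9% (r = 0.5), and shrink the standard error by 0.5% to 13%. These figures rest on the protocol's 10° SD and on an assumed correlation. If r is near 0.1 the improvement is negligible, although the cost is then negligible too. The trial's validity and its stated sample size of 23 per arm are not in question.

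**What to change.** **Analysis wording.** State that the primary between-arm comparison of passive PIPJ extension always includes the participant's uninjured contralateral passive PIPJ extension as a fixed covariate in the ANCOVA or mixed model, whether or not the arms look different on it. State also that the outcome is not analysed as injured minus uninjured.

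**Timing.** Preferably take the uninjured passive reading at the initial visit, where uninjured active motion is already measured. It then precedes treatment, exists for every participant including those lost early, and is not missing for someone who skips week 3 but attends later. If it stays at week 3, add a simple rule for a missing covariate, for example take it at the next visit attended, or impute the mean over both arms combined.

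**Other outcomes.** The same can be done for the other active and passive motion outcomes, total active and total passive motion, and grip, each with its own uninjured value. Uninjured grip is scheduled at week 5, so it needs the same missing-value rule.

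**Cost.** One sentence of analysis text, one degree of freedom and one reading moved earlier. No additional measurement is needed, and the sample size can stay as it is. The downside is that the benefit may be small if the two sides are only weakly correlated.

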### Blinding

Trained assessors will be blinded from group allocation and different to the treating therapist. Prior to the assessment, the patient will be asked to remove their orthosis or buddy loop and will be discouraged from discussing any form of their treatment to the assessing therapist to ensure the blinding.

### Data analysis

Analysis will commence with descriptive statistics. Histograms and descriptive statistics will be used to review the distribution of continuous variables for outliers, skewness and other potential problems. Counts and percentages will be used to review categorical variable for small categories. Scatterplots and side-by-side boxplots will be employed to visually check for associations between variables. Outliers will be checked for data errors and, if legitimate, adjusted for using Winsorizing or trimming. Data transformations will be used to address skewness if required.

Independent samples t-tests will be used review the statistical significance of these differences in means at follow-up. Analysis of covariance (ANCOVA) will be used to adjust for any differences between groups at baseline. Repeated measures analysis of variance (ANOVA-RM) or linear mixed models will be used to model differences between treatment groups over time. Data will be analysed using an ‘intention to treat’ analysis.

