## Abstract

**Background:**

Volar plate injuries are a common hand injury and complications associated with this injury such as a fixed flexion deformity, persistent pain and oedema can have a significant impact on a person’s function. The literature reports these injuries are treated using various splinting materials such as thermoplastic, in varying degrees of proximal interphalangeal joint flexion or buddy loops. Despite volar plate injuries being reported as common, optimal non-surgical treatment of these injuries remains unclear.

This study aims to investigate whether a dorsal blocking orthosis in a neutral position (0^0^) is more effective than buddy loops for a volar plate injury to the proximal interphalangeal joint in preventing a fixed flexion deformity, reducing pain, managing oedema, and promoting function.

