Based on the research available, splinting the PIPJ in a neutral position may result in superior outcomes as it positions the joint in an optimal resting position and allows protected early active motion. Using buddy loops to treat volar plate injuries has been reported to provide good Active Range of Motion (AROM) outcomes due to the early and easy commencement of early active motion, however, could still lead to the development of a FFD due to the natural resting posture of the digit. Due to the limitations in the current literature, further research is required to determine the optimal way to treat these injuries.

The aim of this study is to investigate whether a dorsal blocking orthosis (splint) in a neutral position (0°) is more effective than buddy loops in the treatment of a volar plate injury. Specific hypotheses will address; splinting the PIPJ in a neutral position produces a) a lower average extension contracture of a FFD than splinting in buddy loops; b) lower mean pain scores than buddy loops; c) lower mean oedema measure than buddy loops; and d) splinting the PIPJ in a neutral position results in changed adherence to treatment compared to buddy loops.

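### The rule to Winsorize or trim genuine outliers also covers passive PIPJ extension; if marked flexion deformities occur, it alters or removes the values the primary comparison is about

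*Protocol article*

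**What the plan says.** The Data analysis section opens with a screening step: "Histograms and descriptive statistics will be used to review the distribution of continuous variables for outliers, skewness and other potential problems". The action that follows is stated as settled: "Outliers will be checked for data errors and, if legitimate, adjusted for using Winsorizing or trimming". The section gives no cut-off, does not choose between the two methods, does not say whether outliers are identified in the pooled data or within each arm, and makes no exception for any outcome.

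The same section names the test, "Independent samples t-tests will be used review the statistical significance of these differences in means at follow-up", and the analysis principle, "Data will be analysed using an ‘intention to treat’ analysis".

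Under Outcome measure: "The primary outcome measure will be passive PIPJ extension". The Abstract's aim includes effectiveness "in preventing a fixed flexion deformity, reducing pain, managing oedema, and promoting function", and hypothesis a) in the Background predicts "a lower average extension contracture of a FFD than splinting in buddy loops" for the neutral orthosis.

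**The concern.** Checking outliers for data errors is sound. The difficulty is what happens to values that pass the check: they are still pulled in or deleted. For passive PIPJ extension, a large confirmed deficit is a patient with a marked flexion deformity, which is the outcome the orthosis is meant to prevent. If the benefit lies in fewer such patients, it lies in the tail that the rule acts on.

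Two consequences follow. Trimming removes a randomised participant because of the observed outcome, which cannot be squared with intention to treat. And because the cut-off, the method and the pooled or per-arm choice are open when the histograms are inspected, the same sentence permits handling that hides a real difference and handling that produces significant results too often.

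**Working it through.** **Design figures, reproduced.** From the Sample size section: difference 10°, SD 10°, 5% significance (two-sided assumed), 90% power. The two-sample t-test solution is n = 22.02 per group, rounded up to the stated 23 (power 91.2%). For dropout, 23/(1 − 0.25) = 30.7, so 31; the plan enrols 32 per group, and 32 × 0.75 = 24 completers. The simulation uses 24 per arm.

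**Assumptions not in the documents.** Extension deficit is a mixture: most patients at mean 5° (SD 5°), a deformity subgroup at mean 30° (SD 8°). Outliers are values outside Q1 − 1.5×IQR or Q3 + 1.5×IQR. Trimming deletes them; Winsorizing moves them to the fence. The test is the ordinary t-test at two-sided 5%.

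**Scenario A: deformity in 25% of controls and 5% of the orthosis group.**
- True difference: (0.25 − 0.05) × (30 − 5) = 5.0°.
- Control variance: 0.75×25 + 0.25×64 + 0.25×0.75×25² = 18.75 + 16 + 117.2 = 151.9.
- Orthosis variance: 0.95×25 + 0.05×64 + 0.05×0.95×25² = 23.75 + 3.2 + 29.7 = 56.6.
- Average SD: √((151.9 + 56.6)/2) = 10.2°, close to the plan's 10°.

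| Handling (pooled fences) | Estimated difference | Power |
|---|---|---|
| Values kept | about 4.9° | about 36% |
| Trimmed | about 1.2° | about 11% |
| Winsorized | about 3.5° | about 33% |

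Trimming removes about 5 of the 48 participants. With equal deformity rates, pooled fences leave type I error near 5% for both methods.

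**Scenario B: no treatment effect, deformity in 15-20% of each arm, fences drawn per arm.**

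| Handling (per-arm fences) | Type I error |
|---|---|
| Values kept | about 5% |
| Trimmed | about 16-25% |
| Winsorized | about 11-13% |

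By chance, the fence in one arm catches its deformities while the fence in the other does not, and the t-test's standard error ignores this.

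**Scenario C: normal data at the design values (difference 10°, SD 10°).** The estimate stays at 9.5-10.0° and power at 90-92% (about 92% with values kept).

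**A second mixture as a check** (23 per arm; main group 2°, SD 4°; deformity 30°, SD 6°). With 25% v 5% deformity, 5.6° becomes 0.5° under pooled trimming (rejection rate 41.5% to 7.7%) and 3.2° under pooled Winsorizing. With 40% v 5%, 9.8° becomes 4.4° (power 81% to 36%) and 7.7°. With 15% in both arms, per-arm fences give a type I error of 20.3% (trimming) and 15.2% (Winsorizing), against 5.4% untouched. The pattern is the same; the sizes move with the assumptions.

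**The case against.** The strongest reply is that the rule acts only if legitimate outliers occur, and that in the plan's own design case it does almost nothing (Scenario C). That stands. A reader might infer that the primary estimate and p-value are distorted whatever the data look like; the documents do not support this. Nor is it certain that a fence would flag the deformities. The protocol describes fixed flexion deformity as a common complication, and the commoner it is, the wider the fences. With deformity in 50% v 10% (first mixture, true difference 10°), pooled trimming gives 8.8° with power 71% against 80% untouched, and pooled Winsorizing gives 9.7° with no loss.

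Other stronger readings also fail:
- That a t-test after such handling always has too small a standard error: pooled fences keep type I error near 5%. The inflation belongs to per-arm handling.
- That the whole rule breaks intention to treat: Winsorizing keeps every participant in the allocated arm. Only trimming conflicts.
- That deformity cases vanish from the trial's results: hypothesis a) concerns an average, and complications, recorded at weeks 3, 5 and 8, are not touched by the rule.
- That the sentence "Data transformations will be used to address skewness if required" is a further error: it is conditional and conventional, and its application can be left to the analysis plan.

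It may also be said that a separate analysis plan will supply the details. It could add a threshold and a method. But the protocol has already committed to changing values confirmed as genuine, so this is a rule fixed badly and not a detail left out.

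**Conclusion.** The point holds in conditional form. As written, the plan alters or deletes confirmed genuine values of the primary outcome, and its trimming option contradicts its intention-to-treat statement. If marked deformities occur as a minority of patients, pooled handling can shrink the contrast, from about 5° to 1.2° (trimming) or 3.5° (Winsorizing) in the assumed case, without inflating type I error. Per-arm handling with an ordinary t-test can raise type I error to about 16-25% (trimming) or 11-13% (Winsorizing).

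These sizes rest on the assumed mixture, the 1.5×IQR fence and 24 completers per arm; none of the mixture values comes from the documents. With near-normal data the effect is small. What does not depend on the assumptions is that the rule reaches the primary outcome and that trimming conflicts with intention to treat.

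**What to change.** Replace the outlier sentence with: *Outliers will be checked and verified data errors corrected; all legitimate values will be kept unmodified in the primary intention-to-treat analysis of each outcome. Any Winsorized or trimmed analysis will be a labelled sensitivity analysis with a pre-specified rule and a matching test (e.g. Yuen's).*

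If residuals are clearly non-normal, keep the mean difference in degrees for passive PIPJ extension and take its confidence interval and p-value from a bootstrap or permutation method.

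The cost is one sentence. The confidence interval may be slightly wider when extremes are kept. The sample size stays at 23 evaluable and 32 enrolled per group.
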